## Abstract

**Background:**

Home-delivered meal programs (HDMP), such as Meals on Wheels, offer nutritious meals for homebound older adults experiencing nutritional risk. Despite receiving meals, participants may still have difficulty achieving nutritional goals, overcoming social isolation, and addressing other health issues. We aim to evaluate the impact of adding enhancements to traditional HDMP on improving diet quality, food and nutrition security, loneliness, and health-related quality of life among older adults in a randomized controlled trial.

**Methods:**

Homebound older adults at nutritional risk and participating in the Meals on Wheels of Rhode Island, Inc. (MOWRI) HDMP are randomized to receive either a usual care control group of the traditional HDMP (5 meals delivered per week) or the enhanced program (Meals+), which includes four Community Health Worker (CHW) coaching calls using motivational interviewing, and delivery of three healthful grocery bags during 12 weeks, in addition to the traditional HDMP. The primary outcome is diet quality measured by the validated Dietary Screening Tool (DST). Food and nutrition security, loneliness, and health-related quality of life are secondary outcomes assessed by validated measures. In the 12-week follow-up call, CHWs also ask participants about utilization and satisfaction with the intervention. The usual care group receives coaching from CHWs to connect them to community resources in this follow-up call. Study procedures were tested in a pilot randomized controlled trial (*n* = 12), resulting in modifications to the study protocol.

**Discussion:**

Enhancements such as CHW calls and grocery bags can help HDMP target food access, social and health interventions for older adults. These enhanced HDMP have the potential to be sustained and replicated nationwide.

**Trial registration:**

Number NCT06401694; Start date: 2024-06-20.

**Supplementary Information:**

The online version contains supplementary material available at 10.1186/s12889-025-24080-6.

## Background

Food insecurity is defined as a lack of access to enough food to maintain an active and healthy life [1]. In 2023, 13.5% of households in the United States were food insecure [1]. This number was higher for low-income older adults living alone, with 29% of those living below the poverty line experiencing food insecurity [1]. Among older adults, food insecurity is associated with poorer diet quality and higher rates of chronic disease [2, 3]. Some older adults experiencing food insecurity must choose between spending money on food or medication, which further compromises their health [4].

It is common for older adults to suffer from numerous nutritional deficiencies and have difficulty reaching their daily nutrient intake goals [5]. A longitudinal study among older adults observed that those with food insecurity had significantly lower Healthy Eating Index (HEI) scores, which implies lower diet quality and higher prevalence of nutritional deficiencies [6, 7]. In this sense, many older adults have difficulties in managing their own nutritional needs and could benefit from food programs, such as home-delivered meal programs [4, 8].

Home-delivered meal programs (HDMP) are among the tools used to combat food insecurity among older adults and other at-risk groups [9–12]. Community-based HDMP delivers healthy meals to older adults to improve diet quality and promote independent living, while also providing informal daily well-being checks. This can result in reduced hospitalizations, shorter hospital stays, fewer readmissions, and ultimately, lower healthcare costs [11, 13]. Systematic reviews of observational and intervention studies demonstrate that HDMP may also impact older adults’ quality of life, by reducing frailty, loneliness, and risk factors that exacerbate chronic diseases [10, 14]. The psychosocial benefits of HDMP derive from the interface between the community-based workforce and older adults in their homes, connecting them with food and health services [15–18]. Many older adults have few social ties, which makes the work of HDMP paid and volunteer drivers essential for social interaction through daily informal well-being checks [18, 19].

Despite the benefits, 70% of HDMP recipients do not meet their daily nutritional needs [9]. Some evidence suggests that increasing the number of meals delivered could strengthen the impact of HDMP on energy and protein intake, participants’ satisfaction, and overall diet quality [10, 11]. Evidence from multiple studies shows that providing more than one meal per day, providing meals rich in protein, and nutritional counseling is associated with higher calorie and protein intake among older adults [9, 10, 12].

Similarly, an intervention with low-income older adults living in Rhode Island senior housing demonstrated that increases in fruit and vegetable intake when a mobile produce market selling produce at affordable prices came to the housing sites [20]. This study demonstrates the importance of increasing access to healthier foods for older adults, especially those with mobility difficulties and/or with low income. Therefore, expanding HDMP to include healthy groceries delivered to the home presents an opportunity to enhance nutrition for older adults at nutritional risk.

Adding complementary services beyond meal and food delivery may also be beneficial for recipients of HDMP. One way to enhance HDMP services and their impact on outcomes for older adults is to utilize community health workers (CHWs). Generally, the role of CHWs is based on the community-based workforce, assisting people in overcoming social and financial barriers and, consequently, combating existing disparities [16, 21, 22]. CHWs work to help people connect with an array of services and help prevent health problems, serving as a bridge between individuals and the resources available in the community. Their work is generally focused on low-income individuals and racial/ethnic minorities, which can reduce healthcare inequities [22]. Systematic reviews strongly support the positive impact of the role of CHWs on factors such as depression, loneliness, quality of life, and hospitalizations [15, 17]. A key aspect of CHW support is health coaching. In recent years, robust evidence has demonstrated the effectiveness of CHWs in delivering health information [16]. By including CHWs within organizations that deliver HDMP, CHWs can offer coaching to reduce barriers to healthy eating, provide education and address other social needs faced by older adults.

We describe the protocol for a pragmatic randomized controlled trial in partnership with Meals on Wheels of Rhode Island, Inc. (MOWRI) that aims to test the effectiveness of an enhanced HDMP delivery intervention with two new components - CHW coaching and supplemental grocery bags - on the health and social outcomes of older adults. The trial is rooted in Community-Based Participatory Research (CBPR) with an academic-community partnership between MOWRI and the University of Connecticut researchers evaluating the enhanced HDMP. Research based on CBPR methodology seeks to maintain the subjects of interest at the center of the process, while providing empathy to understand the complex needs and contexts of the individual. CBPR is based on the organization of interdisciplinary teams that allow deeper insights into the sustainability of public health interventions [23].

The CBPR has been shown to strengthen community-research engagement, facilitate understanding of the health issues faced by the community, and identify practical ways to overcome them [24, 25]. Evidence also demonstrates the effectiveness in developing innovative strategies for the older adult population and their specific needs [26–29].

The primary aim of the study is to test whether an enhanced HDMP improves outcomes among older adults. The primary outcome of the study is diet quality. Secondary outcomes include food and nutrition security, loneliness, and health-related quality of life (HRQOL). We hypothesize that clients receiving the enhanced version of the program will demonstrate improvements in these outcomes compared with those receiving only the usual care program, by offering more food, increased social interactions, and an opportunity to connect with additional community resources. This work will advance an understanding of how to increase the impact of HDMP on diet quality and psychosocial outcomes in low-income older adults. This paper represents version 2.0 of the study protocol, finalized on 05/20/2025 (NCT06401694).

## Methods

### Overall study design and population

This is a pragmatic randomized controlled trial with two intervention arms (Fig. 1): a usual care program (home-delivered meals) compared to an enhanced delivery approach (usual care plus grocery bags and CHW coaching calls). All potential MOWRI clients are screened at intake using their usual program eligibility tools including demographics, Nutrition Risk Assessment (NRA) questions, Activities of Daily Living (ADLs), Instrumental Activities of Daily Living (IADLs), living situations, medical conditions, and outside activity. All clients deemed at nutritional risk based on NRA score and meeting other study eligibility criteria undergo a process of informed consent. Those that consent to enroll in the study complete the baseline measures (described below). Then, participants are randomized to usual care or enhanced services (Meals+).

**Fig. 1 Fig1:**
[figure not shown]
Study Flow Diagram

### Eligibility criteria

Study participants are adults 60 years or older who: (1) reside in the state of Rhode Island; (2) can read and speak Spanish or English; (3) are nutritionally at risk as determined by the NRA; (4) are eligible for Title III - funded home-delivered meals assistance. For the pilot study, the NRA score eligibility cutoff was set at ≥ 12. In selecting the NRA cutoff, the study team aimed to enroll participants at high nutritional risk while also considering the expected yield of eligible participants per week given the distribution of clients on the MOWRI waitlist and the team’s capacity to deliver the intervention. This cut-off may be reconsidered based on participant yield in the early stages of the main trial, with the goal of maximizing enrollment while still enrolling participants at high nutritional risk. The exclusion criteria are cognitive or physical limitations that prevent an individual from giving consent or participating in intervention or evaluation activities, as assessed by normal interactions by intake staff or study team at enrollment.

### Ethical considerations and dissemination

The institutional review board (IRB) at the University of Connecticut approved this protocol (BRANY24-073-910). The study underwent an expedited review as it involves no more than minimal risk to the subjects. Given the mode of interactions between participants and the research team, informed consent procedures are administered over the phone with an information sheet sent to the participant. These processes of informed consent approved by the IRB as they were not expected to adversely affect the rights and welfare of the subjects. All study staff (including those at MOWRI) completed the Collaborative Institutional Training Initiative (CITI) Social and Behavioral Research training. This trial is coordinated by the co-principal investigators, with no formal committee. The study protocol follows the 2025 Standard Protocol Items Recommendations for Interventional Trials (SPIRIT) statement [30] (Supplementary File 1).

We will submit all significant protocol modifications to IRB for approval, with modifications to ClinicalTrials.gov if applicable. We will disclose protocol modifications in future publications. We will disseminate results through peer-reviewed publications, formal presentations at international, national and local conferences, and presentations for community stakeholders. Authorship criteria will follow the International Committee of Medical Journal Editors (ICMJE) guidelines [31], with the acknowledgement for contributions for study design development, intervention activities, analysis, and intellectual content review.

### Enrollment and randomization process

Once an eligible client is identified during the initial intake phone call, a CHW gives a brief description of the study and asks if the participant would like to hear more details about the study. Unsure clients are sent information about the study; then the CHW follows up with a phone call as needed. If a client is interested in the study, the CHW verbally walks them through the informed consent script over the phone. If the participant agrees, verbal consent is documented, and a hard copy of the consent information sheet is mailed to the home, if it was not previously mailed. Clients can ask questions at any point during the consent process. After all the clients’ questions have been answered, those who wish to consent indicate that they have understood the study and agree to participate by verbally stating “yes” when asked by the CHW if they would like to enroll. If at any time a client decides that they are not interested in the study, the phone call will conclude, and the client will not be contacted about the study again. However, they can still receive regular home delivered meals from MOWRI.

After participants consent to participate, the CHW conducts the baseline assessment over the phone. This assessment can occur immediately after consent or in a subsequent phone call considering participants’ availability. The baseline assessment includes the following: dietary screening tool (DST), food and nutrition security measures, loneliness and health-related quality of life surveys, demographic questions not included during the routine MOWRI intake process, a health literacy assessment, and an assessment of access to community resources. Participants in both study arms receive a $20 prepaid debit card after completion of the baseline assessment.

Randomization is 1:1, with stratification of participants on living alone vs. living with others. Randomization is performed at the household level and in the case of more than one enrolled client per household, they are randomized to the same study arm. The Research Electronic Data Capture (REDCap) system randomly assigns participants within strata to one of the two conditions after the client completes the baseline survey. The assignment arm is not blinded for study team staff or participants. After randomization, the CHW tells the participant which group they were randomized to and describes the appropriate study arm processes. For participants in the Meals+ intervention group, the CHW describes the upcoming 12-week intervention and asks them to schedule a time for the first CHW coaching session within the next week. For participants in the usual care group, the CHW informs the participant that they will receive the usual MOWRI home-delivered meal service and that they will contact them in about 11 weeks to schedule a time for the 12-week call.

All plans for the design of the intervention and the evaluation were made using a CBPR approach, with decisions made jointly by University of Connecticut researchers and MOWRI leadership and staff, and additional input from community partner stakeholders. The academic-community team met at least weekly to discuss all project-related plans during the development of the intervention and to jointly solve implementation issues that arose during the pilot intervention phase.

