### Enhanced intervention components

#### CHWs

The first component of the Meals+ intervention is support from a certified CHW. The approach for CHW interactions with clients is to assess needs, identify gaps in care and resources, and then help the client through health coaching and resource coordination. Through these interactions, the CHW addresses social determinants of health, improving food and nutrition security through instrumental and social support, and increasing socialization by offering human connection. The coaching is conducted during four calls, which includes a brief form of motivational interviewing (MI), goal setting, and an action plan focused on addressing some of the client’s nutrition, health, or social issues (Fig. 1). At the final call (Week 12), CHW checks in with the client, and makes referrals to the health insurer or other appropriate community resources for any on-going or unmet needs. Then they conduct follow-up measures (diet quality, food and nutrition security, loneliness, and HRQOL) and ask about satisfaction with the intervention. Fig. 1 describes the content of each call. For any of the four coaching calls, if participants are unresponsive to multiple contact attempts from the CHW, that particular call is considered missed. The participants are contacted during the scheduled time for their next call.

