### Evaluation activities

After the 12-week intervention period, participants in both arms are contacted by CHWs for the follow-up outcome assessment. Participants in the Meals+ arm are asked these questions after the Call 4 intervention component has been completed, while participants in the usual care arm are asked these questions before they receive the delayed intervention call content. For both study arms, the CHW asks about satisfaction with the home-delivered meals and the overall study. For the enhanced study arm, the CHW also asks participants about how much food they consumed from the food bags, use of recipes and educational materials, and satisfaction with the intervention. Participants in both arms receive an additional $30 incentive after completing the 12-week follow-up assessment.

Participants in the Meals+ arm are also asked if they might be interested in participating in a post-intervention satisfaction interview. Of the participants who consent, a subset is selected for interviews, aiming to include participants from all CHWs. UConn staff asks MOWRI for the contact information of those selected participants. Post-intervention interviews ask what participants think about the food bags, recipes, communication with CHW, perspectives about changes related to participation in the intervention (including diet, quality of life and eating habits), and strengths and limitations of the intervention. The participants that complete these interviews receive an additional $25 incentive. These interviews are audio-recorded, and the recordings are sent to a professional transcription company to be transcribed.

The Practical, Robust Implementation and Sustainability Model (PRISM) is the evidence-based framework for evaluation activities [45]. We are measuring PRISM domains using key informant interviews with MOWRI leadership and staff, CHWs and external partners; CHW notes from participant calls; participant evaluation surveys; process evaluation data; MOWRI report data; quality control checks of audiotaped CHW calls; nutritional analysis of food bags; cost tracking; and minutes of project meetings.

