### Sample size and power calculations

We conducted a power analysis for this randomized controlled trial (RCT) using Statistical Analysis System (SAS) version 9.4 (Cary, NC). Assuming that the standard deviation for the primary outcome, DST, is 12.0 [48], and a significance level of $$\alpha = 0.05$$ , we will have 80.6% power to detect a difference between the arms of 2.0 points on the DST using 574 participants in each study arm. Because we are expecting 70% retention in each arm we will enroll 1640 participants in the study. We performed this sample size calculation based on assumptions from the literature.

The study uses an intent-to-treat approach so that participants who decline MOWRI program or intervention activities (i.e., deciding not to receive weekly meals from MOWRI, participate in the CHW phone calls, or receive the monthly food bags), remain in the study and will be analyzed according to their assigned intervention. Participants can stop receiving MOWRI services and still receive a follow-up call and continue to be part of the study until follow-up. Participants who are no longer getting home-delivered meals will no longer get the enhanced program of CHW calls or food bags. Participants will be withdrawn from the study if either: (1) they verbally disclose that they no longer wish to participate in the research; (2) they have not had any calls with the CHW by week 8; or (3) if they are in an institutional setting (e.g., hospitalization or inpatient rehabilitation) at the time the follow-up assessment is scheduled to occur, and this stay lasts > 14 days. In addition to the intention-to-treat analyses, we will examine the effects of the intervention among participants who would have complied with and adhered to the assigned intervention using principal stratification analysis [49, 50].

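### Unblinded CHWs collect the self-reported week-12 DST under different conditions in the two arms, so a small arm-specific reporting shift could pass for a diet effect

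*Protocol article*

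**What the plan says.** On masking, the Enrollment and randomization process section states: "The assignment arm is not blinded for study team staff or participants".

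On who measures and when, the CHWs subsection describes the week-12 call in Meals+. The CHW checks in and makes referrals, and after that: "Then they conduct follow-up measures (diet quality, food and nutrition security, loneliness, and HRQOL) and ask about satisfaction with the intervention". Evaluation activities says that "participants in both arms are contacted by CHWs for the follow-up outcome assessment". The same paragraph fixes a different order by arm. Meals+ participants answer once the Call 4 content is finished; usual-care participants answer before the delayed support content begins.

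On the outcome, the Primary outcome subsection describes the DST as 25 questions on dietary intake, based on how often food groups are eaten and scored 0 to 100 with 5 possible extra points.

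On size, Sample size and power calculations gives "80.6% power to detect a difference between the arms of 2.0 points on the DST using 574 participants in each study arm".

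The Discussion says that the randomized design secures attribution of between-group differences to the intervention. Its limitations do not mention reporting or assessor bias.

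**The concern.** Participants cannot be blinded to coaching calls and grocery bags. Who asks the outcome questions, and at what point in the call, is a separate choice that the trial controls. As written, a Meals+ participant reports eating habits to the CHW who has just finished a coaching call. A usual-care participant reports them to a CHW who has not yet offered support. The section on modifications after the pilot adds that the coaching outlines were given anchors pointing to outcome-related topics, so the coaching and the questions cover common ground.

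If these conditions shift the answers, or how they are recorded, by different amounts in the two arms, the difference goes straight into the estimated effect. The target is only 2.0 points, or 0.17 SD (2.0/12), so even a modest differential shift would matter. A positive result near the target could not then be separated from a reporting effect.

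**Working it through.** **Inputs from Sample size and power calculations.** SD 12.0, alpha 0.05, difference 2.0 points, 574 analysed per arm, power 80.6%, retention 70%, 1640 enrolled. Sidedness is not stated. Two-sided is assumed because it reproduces the stated power; a one-sided test would give 88.1%.

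**Step 1: reproduce the plan's figures.**
- SE = 12 × √(2/574) = 0.708.
- Power = Φ(2.0/0.708 − 1.96) = Φ(0.86) = 80.6%, as stated.
- Enrolment = 2 × 574 / 0.70 = 1148 / 0.70 = 1640, as stated.

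The sample size is correct. The issue is measurement only.

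**Step 2: smallest significant difference.** 1.96 × 0.708 = 1.39 points, or 0.12 SD.

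**Step 3: effect of a differential shift.** Let b be an upward reporting shift in Meals+ only, with no true effect. The two-sided rejection rate is Φ(b/SE − 1.96) + Φ(−b/SE − 1.96). The document gives no value for b, so every value below is an assumption.

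| Assumed b (points) | Two-sided rejection rate |
|---|---|
| 0 | 5% |
| 0.25 | 6.4% |
| 0.5 | 10.9% |
| 1.0 | 29.2% |
| 1.39 | 50% |
| 2.0 | 80.6% |

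**Step 4: dependence on the SE.** The planned model uses baseline and follow-up DST, so the actual SE may differ from 0.708. The correlations here are also assumed.
- Baseline-adjusted, SE × √(1 − ρ²). At ρ = 0.5 the SE is 0.613, the threshold is 1.20, and a 1-point shift gives 37%. At ρ = 0.7 the SE is 0.506, the threshold is 0.99, and the rate is 51%.
- Change score, SE × √(2(1 − ρ)). At ρ = 0.3 the SE is 0.838, the threshold is 1.64, and the rate is 22%.

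More precision makes the test more sensitive to a fixed bias, not less.

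**Step 5: does anything in the plan remove the shift?**
- Baseline DST is taken before randomization, so adjusting for it cannot remove a shift that arises at follow-up.
- Multiple imputation addresses missing values, and principal stratification addresses compliance. Neither addresses misreporting.
- The quality checks under Process evaluation review a subset of Meals+ calls for fidelity to call content. No check of DST administration across arms is described.

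**The case against.** The strongest reply is that this is an openly unblinded pragmatic trial, and that CHWs recruit, take baseline measures, announce the allocation and collect follow-up in both arms. Much courtesy bias would then be common to the arms and cancel. This stands: only the differential part matters. The DST is also a set of fixed frequency questions, which limits how far an interviewer's recording can drift. Coaching need not be about diet, since action plans may address health or social needs. The direction is open too, because coaching could make people more critical of their own diet.

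A reader might infer three stronger things that the document does not support.
- That the same CHW coaches a participant throughout and then scores the outcome. This is a reasonable inference, and tracking retention by CHW fits it, but no passage says so. The text supports only that the CHW on Call 4 then asks the DST.
- That the trial has a false-positive rate of 29% or 50%. The shifts are assumed, and the percentages show sensitivity to bias, not its likelihood.
- That a different interviewer would solve the problem. Participants know their arm and have been coached, so the part of the shift that comes from them would remain.

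None of this removes the difference in question order and interviewer role that the protocol fixes between the arms.

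**Conclusion.** The point holds as a weakness in outcome ascertainment. The arms differ at week 12 in what precedes the DST and in the role of the person asking it. With no masking and a self-reported outcome, a differential shift is possible, and neither randomization nor the planned analyses protect against it. The Discussion's attribution statement therefore claims more than the design delivers.

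On the plan's SD of 12 and 574 per arm, 1.39 points is enough for significance. Assumed Meals+-only upward shifts of 0.5, 1.0 and 1.39 points would give about 11%, 29% and 50% false positives when there is no true effect. This rests on a two-sided test, the plan's SE, and shift sizes that the document does not supply. The conclusion is that such a shift could produce a significant result, not that it will.

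**What to change.** 1. In both arms, ask the week-12 outcome block first, from the same fixed script, before any Call 4, satisfaction or delayed-support content.
2. Where the existing rota allows, have the block asked by a CHW who did not coach that participant, with the arm not displayed until the block is closed. Then hand over to the participant's own CHW. The protocol implies more than one CHW, since satisfaction interviewees are chosen "aiming to include participants from all CHWs"; the number is not given.
3. If follow-up is already under way, change both arms on the same date.
4. Qualify the attribution statement in the Discussion and list the residual reporting risk as a limitation.

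Reordering and scripting cost little. Separating coach from asker costs scheduling and a hand-off during the week-12 contact. The plan already states "Because we are expecting 70% retention in each arm we will enroll 1640 participants in the study", so the effect of the hand-off on retention should be watched. Moving about 1,148 interviews to university staff would need extra resource and is not proposed.
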